## Abstract

**Background:**

Cash-based transfer programmes are an emerging strategy in the prevention of wasting in children, especially targeted at vulnerable households during periods of food insecurity or during emergencies. However, the evidence surrounding the use of either cash or voucher transfer programmes in the humanitarian context and on nutritional outcomes is elusive. More evidence is needed not only to inform the global community of practice on best practices in humanitarian settings, but also to help strengthen national mitigation responses.

**Methods/Design:**

The Research for Food Assistance on Nutrition Impact Pakistan study (REFANI-P) sets out to evaluate the impact of three cash-based interventions on nutritional outcomes in children aged less than five years from poor and very poor households in Dadu District. This four-arm parallel cluster randomised controlled trial is set among Action Against Hunger (ACF) programme villages in Dadu District, Sindh Province. Mothers are the target recipients of either seasonal unconditional cash transfers or fresh food vouchers. A comparison group receives ‘standard care’ provided by the ACF programme to which all groups have the same access. The primary outcomes are prevalence of wasting and mean weight-for-height Z-score (WHZ) in children. Impact will be assessed at 6 months and at 1 year from baseline. Using a theory-based approach we will determine ‘how’ the different interventions work by looking at the processes involved and the impact pathways following the theory of change developed for this context. Quantitative and qualitative data are collected on morbidity, health seeking, hygiene and nutrition behaviours, dietary diversity, haemoglobin concentration, women’s empowerment, household food security and expenditures and social capital. The direct and indirect costs of each intervention borne by the implementing organisation and their partners as well as by beneficiaries and their communities are also assessed.

**Discussion:**

The results of this trial will provide robust evidence to help increase knowledge about the predictability of how different modalities of cash-based transfer work best to reduce the risk of child wasting during a season where food insecurity is at its highest. Evidence on costing and cost-effectiveness will further aid decisions on choice of modality in terms of effectiveness and sustainability.

**Trial registration:**

Current Controlled Trials ISRCTN10761532. Registered 26 March 2015.

## Background

Cash-based transfers are fast becoming a standard part of the humanitarian agency toolbox. There is growing interest and use in providing cash or vouchers to vulnerable households who have children at risk of undernutrition during periods of food insecurity or during emergencies [1–4] During these periods the prevalence of acute malnutrition or wasting, due directly to transient nutritional deprivation from deficits in energy intake and/or poor appetite, malabsorption, or loss of nutrients due to disease, will increase unless there are sufficient, and appropriate, mitigation strategies to protect these children. Increased focus on prevention strategies to reduce the global burden of wasting has motivated the use of alternative mitigation approaches such as the use of cash-based transfers [5]. However, there is insufficient empirical evidence to demonstrate that cash-based transfers are an appropriate substitute for food-based interventions to prevent acute malnutrition in children and to understand the circumstances under which these interventions are likely to be effective.

Cash-based transfers can be made as direct cash payments or bank transfers using various modalities such as smart cards, mobile phones, e-wallets and e-vouchers or paper vouchers. Vouchers can be exchangeable for fixed quantities of specific food or non-food items or a service (commodity vouchers), or for cash value - exchangeable for a choice of specified food or non-food items with the equivalent value of the voucher (cash or value vouchers) [6, 7]. It is hypothesised that cash or vouchers can tackle wasting through a number of different pathways [Fig. 1]. However, determining which of these pathways is more important is highly context-specific and evidence surrounding the impact of cash and vouchers on child wasting in humanitarian situations is elusive. As a complex public health intervention the causal density between a cash-based transfer programme and nutrition status is high. There are numerous intermediary factors that make it difficult to know with any predictability how a programme will work. As well as this, very little is known about how cash-based transfers interact with the context in which they are set. Understanding the underlying mechanisms in the causal pathway between cash-based transfers and nutrition status, and a context, is crucial to understanding why an intervention works or not and is necessary in providing useful insights into how the outcomes from such studies could be transferred across different settings and populations.

**Fig. 1 Fig1:**
[figure not shown]
REFANI Theory of Change

Most of the available evidence on seasonal cash and food vouchers compares cash and/or vouchers to food transfers with some evidence on cost-efficiency. Also the main focus has been on food access and utilisation [4], rather than nutritional outcomes. This is thought to be due largely to the lack of nutrition objectives [8, 9] because cash-based transfer programmes are typically designed and implemented with food assistance objectives only [10].

A recent four-country study showed that either cash or a food voucher had a greater impact on improving dietary diversity, and were more cost-effective, compared to in kind food transfers [11]. Further evidence has shown that food vouchers can be more effective than cash grants in improving dietary diversity, as well as being more cost-effective [12]. However, another study in the Democratic Republic of Congo showed no observable differences between households receiving either cash grants or vouchers in food security, household coping strategies or asset ownership, though households receiving cash grants reported greater savings [13]. In terms of cost-efficiency, costs associated with delivering cash and voucher transfers have shown to be considerably lower than food in kind transfers [12, 14, 15], with the implementation of cash grants shown to be more cost-efficient than voucher programmes [13].

Cost-effectiveness is an important measurement of program resource use, complementing evidence on intervention effectiveness and providing valuable economic insights to guide decisions regarding resource allocation and priority setting [16, 17]. At present, there is no robust evidence that compares either cash or voucher programmes on nutritional outcomes or longer-term cost-effectiveness regarding the number of cases of malnutrition averted. The REFANI-P study uses a cluster randomised study design to compare three cash-based transfer modalities in Pakistan and to address the evidence gaps on the effectiveness and cost-effectiveness of cash-based transfers on nutritional outcomes.

## Methods/Design

### Aims and objectives

The overarching aim of REFANI-P is to evaluate three cash-based transfer modalities on nutritional outcomes in children aged less than five years from poor and very poor households in Dadu District, Sindh Province, Pakistan.

This study aims to (1) compare the nutrition status of children receiving either a seasonal unconditional cash transfers or a fresh food voucher with those with access to ACF care only, after 6 months and at 1 year; (2) assess the costs and cost-effectiveness of the different interventions; (3) understand the factors that determine the ways in which households use the different transfers; and (4) explore the role of the different processes involved in the study outcomes and how they interact with the context.

### Study design

This is a longitudinal cluster randomised controlled trial (cRCT), with 4 parallel groups with integral process and economic evaluations. Cluster assignment is by village. This study follows the same group (closed cohort) of eligible households with children (6–48 months at baseline) in each group over one year. The design is one-stage and all eligible children within eligible households are included. The intervention takes place over 6 consecutive months (June to November 2015). Data are collected at baseline (pre-intervention), then each month during the 6 month intervention period, followed by a final data collection at 1 year (6 months post intervention). Eligible children are the unit for analysis and clustering within villages is taken into account.

The study is also designed to understand the factors that determine the ways in which households use the different transfers and explore the role of the different processes influencing the intervention outcomes and how they interact with the context. This is done using a mixed-methods approach within a process evaluation framework developed for cRCTs proposed by Grant et al. [18]. Qualitative data are also being collected to inform data collection tool design (e.g. by informing content and rational piloting) and to help to understand any associations found (or not) within the quantitative analysis.

The study will also provide evidence on the costs of these cash-based interventions, and their cost-effectiveness in preventing cases of acute undernutrition. The study uses qualitative and quantitative methods to assess intervention resource use from a societal perspective, including all direct and indirect costs of the intervention regardless of who incurs them, including implementing organisation, beneficiaries, or partners etc. Cost-effectiveness ratios are calculated using cost data along with outcome data from each intervention arm.

### Ethics and consent

Ethical approval was obtained from the Pakistan National Bioethics Committee on 12^th^ February 2015 (reference number 4-87/14/NBC-170/RDC/2304). The study has approval by the Western International Review Board (11/03/2015). The trial was registered on 26^th^ March; ISRCTN10761532.

Participating households are enrolled after providing written informed consent. The consent form, translated into Sindhi, sets out to explain the study and the procedures. There are no risks associated with participating in REFANI-P and households are informed that they could drop out at any time without any penalty or loss of any benefits from the programme. Confidentiality is guaranteed during the study and no individual quantitative data is released. For the qualitative study permission is gained leading to any publication of individual data collected (including photographs).

### Study setting

The study is set in Dadu District in Sindh Province. The economy in Dadu district is largely agrarian; dependent on crop production, livestock keeping, and agriculture labour. The majority of the population is highly vulnerable to shocks, especially the poorest households, and there are a lack of alternative income sources which are further constrained by lack of opportunities and capital.

About 68 % of the population is classified as poor and very poor households (ACF Household Economy Approach Analysis Report 2013 (HEA)) who have limited access to land. A high proportion of very poor households (87 %) are dependent on incomes from casual labour or self-employment; 90 % of these households are reliant on the markets for food purchase all year long. As a consequence of highly insecure cash incomes and a high reliance on food purchased from markets rather than self-produced, very poor households do not typically meet the average daily recommended caloric intake, consuming 1911 kcal/day instead of 2100 kcal/day. Further, a cross-sectional anthropometric nutrition survey carried out by ACF in Dadu in November 2014, showed that the prevalence of global acute malnutrition (GAM) was approximately 14.3 % (95 % CI 10.8–18.7 %) in children 6–59 months. This is expected to be higher during the summer lean season (June to August), where Dadu also frequently experiences localised flooding and droughts, and high temperatures (above 45 °C). Higher levels of GAM for children from poorer households are also expected.

### Study participants

Villages are selected from three agricultural areas sharing similar livelihoods and geography. Households eligible for the study are identified as poor and very poor (according to wealth ranking criteria) and with a child or children aged 6–48 months (at baseline).

### Recruitment of participants

In order to optimize the interest in the study and ensure meeting sample size requirements, sensitisation about the REFANI-P study is carried out first at village level with village leaders by Field Officers. The Field Officers also conduct a household assessment (household size and asset ownership) in each village to ascertain eligibility of households. After which data enumerators return to the villages and share the details with the village leaders and then visit identified households to share details of the study and get informed consent before collecting baseline data.

### Timeline and procedures

REFANI-P starts with formative research using qualitative methods to help develop quantitative data collection tools. These are then piloted and data enumerators are trained on the questionnaires and data collection techniques, including use of Open Data Kit (ODK) data collection and anthropometry equipment. Anthropometry training is supported by the ACF nutrition team. The timeline is shown in Table 1.

**Table 1 Tab1:** Timeline for REFANI-P

2015			2016/17
Pre-intervention period		Intervention period	Post-intervention period
Jan/May	May/June	June – November	June +
Formative research, training, piloting & village sensitisation	Recruitment & baseline data collection	Monthly quantitative data collection	Endline data collection
		Qualitative data collection	Analysis
		Cost data collection	Reporting

### The interventions

Villages are randomly assigned to 4 groups as follows: 1) intervention group receiving a monthly unconditional cash transfer of 1500 Pakistan Rupees (PKR) (‘standard’ cash), 2) intervention group - receiving a monthly unconditional cash transfer of 3000 PKR (‘double’ cash), 3) intervention group receiving a monthly fresh food voucher with a monetary value of 1500 PKR to be exchanged for fresh foods at specified traders (‘cash voucher’), 4) comparison group receiving no additional intervention beyond the basic ACF care activities provided to all.

The ‘standard’ amount of cash represents the amount that was defined in the HEA analysis, to cover a 10 % shortfall in calories by very poor households, and is similar to the amount disbursed by the national Benazir Bhutto Income Support Programme. The cash transfers are disbursed on a monthly basis by mobile banks that travel to a central location for each of the participating villages. The vouchers are disbursed by the ACF team to participating households. Disbursement to targeted mothers from all households starts in June.

### Standard care

All villages have access to ACF care which provides outpatient treatment for severe acute malnutrition (SAM) for children 6–59 months, micronutrient supplementation for children less than five years and pregnant and lactating women, and behaviour change communication. Key messages focus on the underlying causes of malnutrition, and showcase mother and child nutrition, exclusive breastfeeding, complementary feeding practices, food and water hygiene, and handwashing and sanitation. Additionally these key messages are again delivered to all study participants in group sessions by REFANI-P research mobilisers every month. The key messages are targeted at the mothers/care takers of the eligible children, although other household members are not excluded from access to key messages.

### Outcome measures

Measurements are collected on all study households (household questionnaire) and participants (mother and child questionnaire) at month 0, 1, 2, 3, 4, 5, 6 and 12. Measurements are collected during the week following the receipt of each transfer. The primary outcomes are prevalence of wasting (as measured by WHZ < −2 or the presence of bilateral pitting oedema) and mean WHZ score in children.

Secondary outcomes are:in children - cumulative incidence of wasting, prevalence of SAM (<−3 WHZ), low mid-upper arm circumference (MUAC) (<125 mm & < 115 mm), stunting (<−2 height-for-age z-score) and morbidity (mainly diarrhoea, difficulty breathing/cough, malaria)in mothers and children - mean haemoglobin concentration (Hb g/dL) and prevalence of anaemia (children: Hb <11.0 g/dL; severe anaemia as Hb < 7.0 g/dL; non-pregnant women Hb <12.0 g/dL; pregnant women Hb <13.0 g/dL)in mothers - prevalence of low body mass index (<16, <17, <18.5 kg/m^2^), low height (<145 cm) and low MUAC (<230 mm & <210 mm).

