### Anthropometry

Measures include body weight (kg), height (cm), and MUAC (mm). Weights of both mother and children are measured using the *SECA 874* electronic scale (to 0.1 kg accuracy). Height of children (standing and recumbent) and mothers are measured using the *SECA 250* scale (to 0.1 cm accuracy). Age is assessed by both presentation of birth certificate and recall by the mother/care taker using an events calendar. Standard numerical MUAC bracelets are used to record MUAC to the nearest mm. Measurements are taken twice and the average is recorded. All data enumerators are trained according to international recommendations. Standardised weight-for-height and height-for-age *Z* scores and percentiles are calculated as per the World Health Organisation (WHO) guidelines [19].

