### Sample size

To determine the minimum detectable difference in prevalence of wasting for this sample size the following information was used: 1) estimated prevalence of wasting at baseline (16 %); 2) an estimate of the intra-class correlation coefficient (ICC) from a previous survey (0.02); 3) an estimate of the average cluster size (50); 4) for unequal cluster sizes an estimate of the coefficient of variation of cluster sizes (0.65); 5) significance level at 5 % and power of at least 80 %; 6) a likely dropout rate of 10 %; and 7) the estimated number of eligible children per household (2.2).

The sample size is 632 households per intervention group. This sample size is sufficient to measure a detectable difference of 7 % between the intervention groups and the comparison group post intervention. The sample is powered to detect a 0.19 WHZ difference between the intervention and comparison groups (based on a baseline mean of −1.22 (1.10), from previous data).

Sample size calculations were carried out in Stata (SE version 13.1; StataCorp, Special Edition, College Station, Texas 77845 USA) using the [*clustersampsi*] command.

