### Data collection and management

Three Field Officers are supervising 24 teams, each made up of 1 female and 1 male enumerator. Research Mobilisers are available to help the teams in identifying households and sensitisation about the study.

Quantitative data is collected using ODK software which is a freely available application to design surveys for data collection through smart devices and run on android based platforms. The data are exported into password protected MS Excel on a daily basis and sent to the principal investigator. During the study, children identified with WHZ < −2 (using MOYO charts) [21], MUAC <125 mm and/or oedema are referred to the ACF outpatient treatment programme, whilst remaining in the REFANI-P study. Children with a haemoglobin level < 11.0 g/dl, non-pregnant women <12 g/dl and pregnant women <13 g/dl) are referred for Government of Pakistan nearest health facility for standard treatment.

Qualitative data are being collected by a team of three led by a local lead researcher. Interviews are being recorded then transcribed and translated into English within a week of data collection. The focus group discussions relevant to the cost-effective analysis (CEA) are recorded, transcribed and translated into English. The interviews are also recorded and transcribed and translated if deemed necessary during the course of data collection. Relevant data from the impact study are extracted from the quantitative data set in ODK as described above.

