### Planned statistical analysis

The study will use both quantitative and qualitative data analytical methods and a cost-effectiveness analysis will be done. The key steps for the quantitative data analysis of outcome measurements will be: 1) cluster level analyses using summary measures between the different time points and 2) individual level analyses adjusted for clustering (longitudinal generalised mixed models). Significance will be assessed at *p* < 0.05 level.

Baseline descriptive analyses will be carried out on all independent variables at cluster and individual levels to assess baseline differences between groups. The data will be examined for outliers, normality and missing data. To test the overall effect of the interventions (on an intention-to-treat basis), changes in outcome variables between the different groups over follow-up measurements (6 months and at 1 year) will be compared. The interventions, measurement time and intervention-time interaction will be included as fixed effects in the models. Children, mothers and villages will be included as random effects in the intercept and in the slope of the different repeated measurements. Potential confounders (e.g. sex, age and baseline nutrition status) will be used if there are differences at baseline. Best fit of the data will be assessed using maximum likelihood ratio tests.

We will examine the data to determine the extent and type of differential attrition, and depending on our findings, we may apply an appropriate adjustment to estimates of intervention effect and/or discuss the possible consequences they may have on the reliability of the estimates. Since there will be more than one child per household in many cases, a secondary analysis using one child per household (selected at random) will be carried out to confirm if results are being driven by a smaller number of larger households. A mediation analysis (using seeming unrelated regression methods [22–24]) will be carried out to measure the extent to which increased mediating variables may mediate the relationship between the different interventions and comparison group and wasting. All quantitative analyses will be carried out in Stata 13.1. Z-scores will be generated using the World Health Organisation (WHO) macro for Stata.

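### Bilateral pitting oedema counts towards wasting but not towards SAM, so a child with oedema and WHZ at or above −3 is a wasting case that can never be a severe one

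*Protocol article*

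**What the plan says.** The Outcome measures section of the protocol article names two primary endpoints: "prevalence of wasting (as measured by WHZ < −2 or the presence of bilateral pitting oedema) and mean WHZ score in children". Oedema alone therefore makes a child a wasting case, whatever the WHZ.

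The list of secondary outcomes in the same section has "prevalence of SAM (<−3 WHZ", with no oedema term. Low MUAC (below 125 mm and below 115 mm) is listed there as a separate outcome. Oedema is not.

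Table 2 schedules oedema at baseline, at months 1 to 6 and at month 12, the same visits as weight and height.

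On Z-scores, the Anthropometry section says that they "are calculated as per the World Health Organisation (WHO) guidelines [19", and Planned statistical analysis adds: "Z-scores will be generated using the World Health Organisation (WHO) macro for Stata". Neither section says what happens to WHZ at a visit where oedema is present.

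**The concern.** The two case definitions do not nest. One would expect the severe category to be built on the same criteria as the wider one, with a stricter WHZ cut-off. Here a criterion that is sufficient for the wider category is dropped from the severe one. An oedematous child with WHZ at or above −3 shows up only inside the wasting composite, and no other listed outcome picks the child up as severe.

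This is a definition that the article states, not a detail left for the analysis plan. At stake is a secondary outcome: the reported prevalence of SAM would be too low if readers take the label to cover all SAM. SAM by WHZ is uncommon on the planning figures, so even a few oedema cases could be a noticeable share. The comparison between arms is affected to the extent that oedema frequency differs between arms, or follows a different pattern from WHZ below −3.

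**Working it through.** **Definitions side by side**

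| Child | Wasting outcome | SAM outcome |
|---|---|---|
| WHZ < −3, with or without oedema | case | case |
| −3 ≤ WHZ < −2, oedema | case | not a case |
| WHZ ≥ −2, oedema | case (on oedema alone) | not a case |

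**The plan's own figure.** Inputs from the Sample size section: 632 households per group, 2.2 eligible children per household, 10% dropout, mean cluster size 50, coefficient of variation 0.65, ICC 0.02, mean WHZ −1.22 (SD 1.10). Two-sided 5% is assumed, and the same ICC is assumed for WHZ.

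- Design effect = 1 + ((0.65² + 1) × 50 − 1) × 0.02 = 2.4025.
- Children per arm = 632 × 2.2 × 0.9 = 1,251. Effective number = 1,251 / 2.4025 = 520.9.
- Detectable difference at 80% power = (1.960 + 0.842) × 1.10 × √(2 / 520.9) = 0.191.

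The stated 0.19 is reproduced and serves below as the yardstick for mean WHZ.

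**SAM by WHZ alone, normal model**

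- With mean −1.22 and SD 1.10: Φ((−3 + 1.22) / 1.10) = Φ(−1.618) = 5.3%. The same model puts 23.9% below −2, more than the 16% wasting prevalence in the plan, so a second value is needed.
- With the mean set so that 16% fall below −2: mean = −2 + 0.994 × 1.10 = −0.906, and Φ((−3 + 0.906) / 1.10) = Φ(−1.904) = 2.8%.

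**Share of SAM cases missed.** Let p be oedema prevalence and s the prevalence of WHZ < −3. With no overlap, the share of all SAM cases (WHZ < −3 or oedema) that is missed is p / (p + s). The article gives no p; 0.2% to 1.0% is an assumption.

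| | s = 5.3% | s = 2.8% |
|---|---|---|
| p = 0.2% | 0.2 / 5.5 = 3.6% | 0.2 / 3.0 = 6.7% |
| p = 1.0% | 1.0 / 6.3 = 15.9% | 1.0 / 3.8 = 26.3% |

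In children, with 1,251 per arm: about 2.5 (0.2%) to 12.5 (1.0%) oedema cases at one visit, against about 35 (2.8%) to 66 (5.3%) SAM cases by WHZ.

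Overlap lowers these shares. If half of the oedematous children also had WHZ < −3, the extremes become 0.1 / (5.3 + 0.1) = 1.9% and 0.5 / (2.8 + 0.5) = 15.2%.

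**Mean WHZ, only if weights at oedema visits are kept.** The shift in an arm's mean is p × b, where b is the assumed rise in WHZ from fluid. With p = 1% and b = 1 Z it is 0.01, or 5.3% of 0.19. Over wider assumptions (p from 0.1% to 2%, b from 0.5 to 2 Z) it runs from 0.0005 to 0.04, or 0.3% to 21% of 0.19. The shift in the difference between arms is smaller still unless oedema differs by arm.

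**The case against.** The best defence is that the article labels this outcome openly as a WHZ cut-off. That is clear and reproducible, and no oedema case is lost to the trial because oedema counts in the primary wasting outcome. Calling the rule an undercount needs a definition of SAM that includes oedema, and the article does not supply one. This stands in part. It is why relabelling is an acceptable remedy, and why the size above is given relative to WHZ < −3 or oedema. It does not remove the mismatch between two definitions in one section.

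Two stronger readings are tempting, and the article does not support either.

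- *That the trial itself classes oedema as SAM.* A reader might infer this because Standard care describes the programme as outpatient treatment for SAM, and Data collection and management says that children with "MUAC <125 mm and/or oedema are referred to the ACF outpatient treatment programme, whilst remaining in the REFANI-P study". But that sentence sends children with WHZ below −2 or low MUAC to the same programme, so referral does not identify SAM.
- *That oedema-inflated weights enter mean WHZ, so that one child counts as ill in one primary outcome and better nourished in the other.* The article is silent. It defers to the WHO guidelines and the WHO macro, whose handling of oedema cannot be checked here, and the detail may well sit in the full protocol or analysis plan. Nor is it a contradiction for a composite case definition and a continuous mean to treat one child differently.

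**Conclusion.** The point holds for the SAM definition and is minor. As written, oedema makes a child wasted but cannot make the child severe. If SAM is read as including oedema, about 4% to 26% of cases would be missed. That range rests on an assumed oedema prevalence of 0.2% to 1.0%, on no overlap with WHZ < −3, and on a normal model for WHZ. Overlap or rarer oedema makes it smaller.

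The outcome is secondary and the wasting outcome is unaffected. For mean WHZ no error is shown. The effect is conditional on how WHZ at oedema visits is handled, and is about 0.01 in an arm's mean at 1% oedema and a 1 Z rise.

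**What to change.** In Outcome measures, define the SAM outcome as WHZ < −3 or bilateral pitting oedema. Alternatively keep the present rule and rename the outcome severe wasting by WHZ, so that it is not read as all SAM. Either is a one-line change. The first uses oedema data already scheduled at every visit, so nothing new is measured.

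For mean WHZ, add at most one sentence on how visits with oedema are handled and a sensitivity analysis that leaves them out. Do not exclude them from the primary analysis: oedema arises after randomisation and is part of the other primary outcome, so exclusion would make missing WHZ depend on outcome status within an intention-to-treat comparison. The cost is one extra model run.

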### Biochemical measures

Haemoglobin (Hb) g/dl is measured using the *HemoCue 201+* analyser (to 0.1 g/dl accuracy) and adjusted for pregnancy in women [20].

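### Low maternal height is listed as an outcome but measured only before the intervention, and low maternal BMI carries no pregnancy condition, so as written gestational weight dilutes it

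*Protocol article*

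**What the plan says.** The Outcome measures section of the protocol article gives three maternal anthropometric outcomes. The entry begins "in mothers - prevalence of low body mass index", with cut-offs at 16, 17 and 18.5 kg/m², and continues with "low height (<145 cm) and low MUAC (<230 mm & <210 mm". No pregnancy condition is attached to any of them.

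The same section says that measurements on households and participants are collected "at month 0, 1, 2, 3, 4, 5, 6 and 12", without exceptions. Table 2 is more specific. Mother's weight and MUAC are marked at baseline, months 1 to 6 and month 12, while mother's height is marked at baseline only. Pregnancy is marked at every visit.

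Study design places the baseline before the intervention: "Data are collected at baseline (pre-intervention), then each month during the 6 month intervention period". Under Planned statistical analysis, the overall effect is tested as follows: "changes in outcome variables between the different groups over follow-up measurements (6 months and at 1 year) will be compared".

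Haemoglobin is treated differently from BMI. The anaemia outcome has separate cut-offs, "non-pregnant women Hb <12.0 g/dL; pregnant women Hb <13.0 g/dL", and Biochemical measures says that haemoglobin is "adjusted for pregnancy in women".

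**The concern.** An outcome must be observable after the intervention starts and must be able to change because of it. Low maternal height meets neither condition. Its single value comes before the first transfer, and adult height is essentially fixed over a year. A table of low height by arm would describe baseline balance, whatever heading it carried.

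The BMI problem is milder. Weight gained in pregnancy can lift a thin woman above a cut-off, and delivery can bring her back below it, in both cases without any change in her nutritional status. If pregnant women are scored, they contribute little or no information on the effect, and a difference in pregnancy share between arms would appear as a difference in low BMI. At stake is the reading of the maternal secondary outcomes, not the trial's main result.

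**Working it through.** **Low height.** No arithmetic is needed.

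- Outcome measures: low height is a secondary outcome.
- Table 2: mother's height has one measurement, at baseline.
- Study design: baseline is before the intervention.
- Planned statistical analysis: effects are changes at 6 months and 1 year.

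With one pre-intervention value per mother, there is no change to compare. If the baseline value were carried forward, the change would be zero for every mother by construction. The general schedule sentence in Outcome measures also disagrees with Table 2 for this item. Resolving that in favour of repeated measurement would gain nothing, since the quantity does not move.

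**Low BMI.** The article states no prevalence of low BMI or of pregnancy, so there is no figure to reproduce. All inputs below are assumptions for illustration.

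*Dilution.* Let f be the share of mothers pregnant at a visit and RD the risk difference between arms in low-BMI prevalence.

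RD(all) = (1 − f) × RD(non-pregnant) + f × RD(pregnant)

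Assume RD(non-pregnant) = 5 points and RD(pregnant) = 0:

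| f | RD(all), points | Share of effect lost |
|---|---|---|
| 5 % | 0.95 × 5 = 4.75 | 5 % |
| 10 % | 0.90 × 5 = 4.5 | 10 % |
| 20 % | 0.80 × 5 = 4.0 | 20 % |

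The loss is smaller if pregnant women's BMI category also responds to the transfers.

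*Bias from unequal pregnancy shares.* With Δf the difference in pregnancy share between arms:

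bias = Δf × (prevalence in pregnant − prevalence in non-pregnant)

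| Δf | Non-pregnant | Pregnant | Bias, points |
|---|---|---|---|
| 2 points | 20 % | 10 % | 0.02 × (10 − 20) = −0.2 |
| 2 points | 30 % | 5 % | 0.02 × (5 − 30) = −0.5 |
| 5 points | 20 % | 10 % | 0.05 × (10 − 20) = −0.5 |
| 5 points | 30 % | 5 % | 0.05 × (5 − 30) = −1.25 |

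The arm with more pregnancies looks better by about 0.2 to 1.3 points.

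*How large a chance imbalance is plausible?* From the Sample size section: 632 households per arm, average cluster size 50, 2.2 eligible children per household, coefficient of variation of cluster size 0.65, ICC 0.02. Assume one mother per household, about 50 / 2.2 ≈ 23 mothers per village, and that the ICC for wasting also applies to pregnancy.

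- Design effect = 1 + ((0.65² + 1) × 23 − 1) × 0.02 ≈ 1.63.
- SE of the arm difference at 10 % pregnant = √(2 × 0.10 × 0.90 / 632 × 1.63) ≈ 2.2 points.
- SE at 20 % pregnant = √(2 × 0.20 × 0.80 / 632 × 1.63) ≈ 2.9 points.

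A 2-point difference is thus within one SE, and a 5-point difference is about 1.7 to 2.3 SE, the edge of what chance would give. A 10-point difference would be about 3.5 to 4.6 SE.

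**The case against.** On height, the harm is limited. The planned test uses changes at follow-up, so low height simply drops out of it, and the plan nowhere proposes to report a baseline imbalance as an effect. Height is needed once to compute BMI, and Table 2 also lists child age and sex in its outcomes block, so the labelling there is loose. This makes the error cheap but does not remove it: the item is still named as an outcome and cannot be one.

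On BMI, a reader might infer three stronger things, none of which the document supports.

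- *That BMI, like height, cannot measure an effect.* Weight is taken at every visit, so BMI can change and be compared. Under the assumptions above, 80–95 % of an effect survives.
- *That the plan states pregnant women are scored.* It does not. Their inclusion follows from unqualified wording in a condensed article, and the full protocol or analysis plan, not shown, may restrict the analysis. What stands against this is the article's own practice: where pregnancy mattered for haemoglobin, it was written into the definition, and for BMI it was not.
- *That pregnancy imbalance could shift the result by several points.* That would need a difference between arms well beyond what chance produces in this randomised design. A pregnancy mix that changes over the year changes in every arm and does not by itself bias the comparison.

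Maternal MUAC, already a listed outcome at every visit, also gives a maternal measure that does not depend on body weight.

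**Conclusion.** The point holds in two parts of unequal weight. Low maternal height cannot show an intervention effect. This follows from Table 2 and the planned analysis alone and rests on no assumption. Low maternal BMI is measurable, but its definition as written leaves it open to dilution and a small bias: about 5–20 % of an effect lost, and roughly 0.2–1.3 points of bias. Those ranges rest on assumed values: 5–20 % of mothers pregnant, no effect on BMI category in them, pregnancy shares differing by 2–5 points between arms, and low-BMI prevalence of 20–30 % in non-pregnant against 5–10 % in pregnant women. Both parts concern secondary outcomes only.

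**What to change.** 1. Move low maternal height from the secondary outcomes to the baseline characteristics. Keep the single baseline measurement, which BMI needs, and align the general schedule sentence in Outcome measures with Table 2.
2. Define the BMI outcomes for women not pregnant at the visit in question, using the pregnancy item already recorded at each visit.
3. Keep MUAC as the maternal outcome that covers all women, pregnant or not.
4. Report pregnancy prevalence by arm at each visit.

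No new data are needed, only wording changes and a filter. There are two costs. The BMI analysis loses the women pregnant at each visit, 5–20 % under the assumed range. Pregnancy status after baseline is also a post-randomisation variable: if the transfers affected pregnancy, the restricted comparison would no longer be fully protected by randomisation. Step 4 lets readers judge whether that is a concern, and the MUAC outcome provides a comparison without the restriction.
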